## Abstract

**Background:**

Management of inoperable chronic thromboembolic pulmonary hypertension (CTEPH) remains a clinical challenge. Currently, riociguat, a soluble guanylate-cyclase stimulator is recommended by international guidelines. More recently, balloon pulmonary angioplasty (BPA) develops as an alternative treatment for inoperable CTEPH.

**Method:**

This study is a single-center randomized controlled trial. Subjects with inoperable CTEPH are randomized into either a BPA combined with riociguat or riociguat monotherapy group (2:1) and observed for 12 months after initiation of treatment. The primary endpoint is the change in pulmonary vascular resistance from baseline to 12 months after initiation of treatment. The secondary endpoints include 6-min walk distance (6MWD), WHO-FC, NT-proBNP, SF-36, and other hemodynamic parameters. Safety endpoints are analyzed too.

**Discussion:**

This study aims to compare the efficacy and safety of BPA combined with riociguat and riociguat monotherapy for inoperable CTEPH.

**Trial registration:**

Chinese Clinical Trial Registry ChiCTR2000032403. Registered on 27 April 2020.

## Background

Chronic thromboembolic pulmonary hypertension (CTEPH) is a complex chronic disease. Pulmonary artery stenosis or obstruction caused by organized thrombus can lead to increased pulmonary artery pressure and pulmonary vascular resistance, ultimately triggering progressive right heart failure and death [1]. As a serious long-term complication of acute pulmonary embolism, its exact mechanism is not fully understood and the prognosis is extremely poor. The 5-year survival rate of untreated CTEPH patients with a mean pulmonary artery pressure > 40 mmHg is 30%, while it is only 10% in CTEPH patients with a mean pulmonary artery pressure > 50 mmHg [2]. Currently, the treatment of the CTEPH is limited, mainly including pulmonary endarterectomy (PEA), target treatment medications, and balloon pulmonary angioplasty (BPA) [3–5].

PEA is an established curative treatment and is recommended for patients with operable CTEPH as the first choice by the European Society of Cardiology/European Respiratory Society (ESC/ERS), Cologne Consensus, and Chinese Pulmonary hypertension diagnosis and treatment guidelines (I, C) [3–5]. Nevertheless, 20-40% of patients are deemed unsuitable for PEA surgery due to comorbidities and other factors, and nearly half of the operated patients have residual or recurrent pulmonary hypertension [6–8].

Riociguat, a soluble guanylate-cyclase (sGC) stimulator, has a direct stimulating effect on sGC, which is independent of nitric oxide (NO) level. Meanwhile, it also increases the sensitivity of sGC to NO [9]. These two effects increase the level of cyclic guanosine monophosphate (cGMP), which induces vasodilation and suppresses vascular remodeling, inflammation, and platelet aggregation [10]. Riociguat gets FDA approval in inoperable or persistent/recurrent CTEPH based on the findings of a multicenter randomized clinical trial (CHEST-1) [11] and its extension study (CHEST-2) [12].

BPA is a catheter-based treatment, which is also reported to be effective for inoperable CTEPH [13–17]. After more than 30 years of development and refinements, emerging evidence confirms its role in patients with inoperable CTEPH or residual/recurrent pulmonary hypertension with acceptable complications and comparable long-term prognosis to PEA. Therefore, BPA is a promising alternative treatment for patients with CTEPH and is recommended by the current guidelines for the treatment of inoperable PEA surgery or persistent/recurrent CTEPH after PEA (IIb) [3–5]. However, the modified BPA technology also has certain limitations. It cannot expand distal diffuse pulmonary vascular disease and cannot stop pulmonary vascular remodeling; meanwhile, medications have a very strong effect on mechanical obstruction caused by micro-thrombosis, suggesting that medications and BPA have a different mechanism on the treatment of CTEPH, and the combination of the two methods may be better to further improve CTEPH patients’ outcomes.

The aim of this study is to evaluate the efficacy and safety of BPA combined with riociguat for inoperable CTEPH over 12 months. The results of this study may aid in optimizing treatment selection and improving patient outcomes.

### Hypotheses

The primary hypothesis for the trial is:
For PEA-inoperable patients, BPA combined with riociguat significantly improves hemodynamic parameters including pulmonary vascular resistance compared with riociguat alone.

The secondary hypotheses are:
BPA combined with riociguat significantly improves activity tolerance including 6-min walk distance, WHO functional class, SF-36 compared with riociguat alone.BPA combined with riociguat does not have serious adverse events compared with riociguat alone. It has good safety and tolerance.

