## Methods and analysis

### Design

This study is a singer-center, prospective, randomized controlled trial. As shown in Fig. 1, subjects willing to consider enrollment are consented prior to invasive evaluation. Subjects undergo V/Q scan, right-heart catheterization, and pulmonary angiography for definitive diagnosis of CTEPH by the standard practice based on ESC guideline recommendation [3]. The identified CTEPH patients are provisionally enrolled in this study. An independent experienced PEA surgeon determines if subjects are eligible for PEA. If the subjects are deemed technically operable, they are excluded from this study. All patients who meet the inclusion criteria but don’t meet the exclusion criteria are randomly divided into two groups with 2:1 rate via a randomization application and are observed for 12 months. One group is treated with riociguat only, namely the riociguat group (R group); the other group is given additional BPA therapy on the basis of 3 months riociguat treatment, which is riociguat + BPA group (R+B group). Riociguat tablets are administered orally to all randomized patients at starting dose of 1.0 mg TID and are increased by 0.5 mg increments in 2-week intervals to 1.5, 2.0, and 2.5 mg TID (maximum total daily dose: 7.5 mg) if systolic blood pressure (SBP) is ≥ 95 mmHg and there are no signs or symptoms of hypotension. If higher doses are not tolerated, patients are maintained on lower doses (minimum allowed dose: 0.5 mg TID). After the end of the 8-week titration phase, riociguat is continued at the optimal individual dose for 4 weeks. In the R+B group, patients receive 4 times BPA in 2–3-week intervals in the following 3 months according to the morphology of the pulmonary lesion evaluated by preoperative right-heart catheterization and pulmonary angiography. In general, 3 vessels are performed each time. However, at least among the collaborative institutions included in this study. PEA-inoperable patients are very rarely considered unsuitable for BPA, because the institutes are professional BPA centers in China. Then all participants are followed up to 12 months. And the safety follow-up is up to 30 days later the study completion.

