### Sample size

Previously, BPA shows to result in reducing pulmonary vascular resistance from 7.3±3.2 WU to 3.8±1.0 WU (mean ± SD) within 6 months [15], while riociguat is reported to decrease pulmonary vascular resistance by 2.83±3.1 WU [6]. Based on these studies, it is assumed that the change in mean pulmonary vascular resistance from the start of treatment to 12 months after treatment would be − 4.5 WU for the BPA+R group and − 2.8 WU for the R group, with SD of 2 and 2, respectively. The minimum sample size requires to achieve a significance of 0.05 from a two-sided test with a statistical power of 90%. The combination group is determined to be 54 subjects, and the riociguat group is 27 subjects, for a total of 81 subjects. We estimate the dropout rate to be 15%.

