### Statistical analysis

Data analysis is performed by a specific specialized investigator who keeps being blind to the trial. The research measurement data are presented as mean ± standard deviation, and count data are presented as frequency or percentage. In the baseline characteristics of patients, count data are compared using Pearson’s *χ*^2^ test or Fisher’s exact test and measurement data are compared using *t* test. For primary analysis, the least square means difference and 95% CI for change of pulmonary vessel resistance between groups at 12 months are estimated using analysis of covariance adjusted for allocation factors. For patients who withdraw from the study, the last observation carried forward (LOCF) before withdrawal is used for statistical analysis. Adverse events are evaluated during the safety analysis. The frequencies of adverse events are compared using Fisher’s exact test. We consider the *p* value < 0.05 of two-sided test to be statistically significant. All statistical analysis is performed using SPSS software V22.0. The statistical analysis plan is developed by the principal investigator and biostatistician before the completion of patient recruitment and data fixation.

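### The safety hypothesis claims no excess of serious harm, but the only between-arm adverse-event analysis stated is a test of difference that cannot support such a claim at 54 vs 27 patients

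*Protocol article*

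**What the plan says.** Protocol article, Hypotheses: one of the secondary hypotheses is that "BPA combined with riociguat does not have serious adverse events compared with riociguat alone. It has good safety and tolerance". No margin, acceptable event rate or other criterion goes with it.

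Protocol article, Statistical analysis: "The frequencies of adverse events are compared using Fisher’s exact test", and the general criterion is "We consider the *p* value < 0.05 of two-sided test to be statistically significant". The section plans a 95% confidence interval for the primary endpoint but mentions none for adverse events. It does not name serious adverse events separately.

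Protocol article, Sample size: "The combination group is determined to be 54 subjects, and the riociguat group is 27 subjects, for a total of 81 subjects". The number is derived from the change in pulmonary vascular resistance alone.

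Protocol article, Outcome measure, Table 2: the safety evaluation covers the frequency of named adverse events, clinical worsening and time to it, and laboratory tests. It has no separate item for serious adverse events.

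**The concern.** The hypothesis and the test point in opposite directions. The hypothesis asserts that adding BPA brings no serious harm beyond riociguat alone. Fisher's test takes equality as its null hypothesis and can only produce evidence against it. Two readings of the hypothesis are possible, and neither works:

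- Read literally, as no serious adverse events on the combination, it is refuted by the first such event and needs no test.
- Read as no more serious events than on riociguat alone, the only statistical support that the stated comparison can offer is a p-value above 0.05. In a trial of this size that is a weak finding.

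The trial adds an invasive procedure to a drug, and safety is a stated aim beside efficacy. If a p-value above 0.05 were taken as support for the hypothesis, a sizeable excess of serious events could sit behind a statement of good safety.

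**Working it through.** **Inputs from the article.** Arms of 54 (combination) and 27 (riociguat); two-sided 0.05; Fisher's exact test; 15% dropout. For the sample size: "4.5 WU for the BPA+R group and − 2.8 WU for the R group, with SD of 2 and 2, respectively" (the first figure is a fall, so the difference is 4.5 - 2.8 = 1.7 WU), and "a significance of 0.05 from a two-sided test with a statistical power of 90" percent.

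**Assumptions.** The article gives no serious adverse event rates. All rates below are assumed, and a range is shown.

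**1. What the 81 patients were sized for.** Two-sample t-test (noncentral t), difference 1.7, SD 2, allocation 2:1:
- 22 + 44 gives 89.4% power and 23 + 46 gives 90.7%, so 69 evaluable patients are needed.
- 69 / 0.85 = 81.2, in line with the stated 81.

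The sample size therefore reproduces from the primary endpoint. On this reading it already contains the dropout allowance, and safety plays no part in it.

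**2. A result that is not significant.** Take 7/54 vs 0/27, with 7 events among 81 patients in all.
- Probability that all 7 fall in the combination arm: C(54,7)/C(81,7) = 0.0509.
- Outcomes in the other direction that are no more probable (0, 1 or 2 of the 7 in the combination arm): 0.0003 + 0.0046 + 0.0332 = 0.0381.
- Two-sided p = 0.0509 + 0.0381 = 0.089.

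Newcombe 95% interval for the difference, 7/54 - 0/27 = 0.130:
- Wilson limits are 0.064 to 0.244 for 7/54, and 0 to 0.125 for 0/27.
- Lower limit: 0.130 - √[(0.130 - 0.064)² + (0.125 - 0)²] = -0.011.
- Upper limit: 0.130 + √[(0.244 - 0.130)² + 0²] = 0.244.

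The result is not significant, yet it is compatible with an excess of about 24 percentage points.

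**3. Smallest significant excess.**

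| Events on riociguat | Fewest events on combination for p < 0.05 | p |
|---|---|---|
| 0/27 | 8/54 (15%) | 0.047 |
| 1/27 | 13/54 (24%) | 0.028 |
| 2/27 | 15/54 (28%) | 0.043 |

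**4. Exact power of Fisher's test.** This sums, over all pairs (x, y) with p < 0.05, the product of the two binomial probabilities. The second column of results applies the 15% dropout: 54 × 0.85 ≈ 46 and 27 × 0.85 ≈ 23.

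| Assumed rates, combination vs riociguat | 54 vs 27 | 46 vs 23 |
|---|---|---|
| 10% vs 5% | 4.5% | 3.0% |
| 15% vs 5% | 16.5% | 14.7% |
| 20% vs 5% | 34.3% | 34.4% |
| 20% vs 10% | 13.0% | 14.3% |
| 30% vs 10% | 49.1% | 42.3% |

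Power after dropout is mostly similar or lower. The small rise at 20% vs 10% comes from the discreteness of the exact test. A true doubling from 5% or 10% would be missed in about 95.5% or 87% of such trials at full size.

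**5. Would a formal margin help?** Illustrative non-inferiority size with equal true rates p, margin m, one-sided 0.025, 80% power and 2:1 allocation: riociguat arm n = 1.5 p(1 - p)(1.96 + 0.84)² / m².
- p = 5%, m = 10 points: 56 + 112 = 168.
- p = 10%, m = 10 points: 106 + 212 = 318.
- p = 10%, m = 15 points: 48 + 96 = 144.

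All exceed 81.

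**The case against.** **No rule for p > 0.05 is stated.** A reader might infer that a non-significant Fisher test will be declared proof of safety. The article does not say so. It applies the test to adverse events in general and does not tie it to the safety hypothesis. This objection stands, and the point is limited accordingly: the result could be read that way, and no other between-arm criterion is given.

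**Other safety evidence exists.** Under Adverse events, clinically significant findings are examined for a causal link to BPA or riociguat and recorded. Table 2 adds clinical worsening and laboratory tests, and count data are to be presented as frequencies or percentages. So procedural harm would not go unseen, whatever the p-value. This stands, but none of it supplies a criterion for the claim of no excess.

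**Dilution by the shared riociguat phase.** Both arms have the same drug treatment for the first three months, and a reader might infer that events are pooled over the year and the BPA effect diluted. The article fixes no analysis window, adverse events are collected at each visit, and a split by period may properly be left to the analysis plan. This is not an error in the article.

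**Procedural injuries in one arm only.** A reader might also infer that perforation, dissection and rupture can arise only with BPA. Table 2 lists them in brackets under hemoptysis and pulmonary hemorrhage, which can occur in either arm, and both arms undergo right-heart catheterization. The text does not support "only".

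**Low power for safety is usual.** Most trials sized on efficacy share it, and the Sample size section claims no power for safety. That is fair. The fault lies in attaching a hypothesis of no harm to such a trial.

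**Conclusion.** The point holds in a limited form. The article states a hypothesis of no excess serious harm and one between-arm adverse-event comparison, and the second cannot confirm the first. The mismatch is in the published text, so it is more than detail left to an analysis plan.

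Its size can be seen without assuming any rate: an observed 13% against none is not significant, and its interval reaches +24 points. The power figures do rest on assumed rates and on 54 and 27 patients being analysed. Within the range shown, power stays below 50% even when the true rate triples from 10% to 30%.

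The primary endpoint, its analysis of covariance and the sample size are unaffected. The article does not support the stronger conclusion that the trial will report harm as safety. What is affected is any conclusion of good safety that rests on the Fisher test.

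**What to change.** Restate the safety hypothesis as an estimation objective. In Statistical analysis, add that the risks of serious adverse events and of BPA complications will be reported per arm, with the risk difference and its 95% confidence interval. State that a non-significant Fisher test will not be taken as evidence of equal or good safety.

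A split at month 3 and a per-procedure complication rate in the combination arm would be informative. They are optional additions, not corrections of an error.

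Pre-specifying a non-inferiority margin instead is not realistic with 81 patients under the assumptions shown.

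The cost is the rewording of one hypothesis and a short addition to the safety analysis, with no further patients. The price is a weaker safety claim, but one that the data can support.

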## Methods and analysis

### Design

This study is a singer-center, prospective, randomized controlled trial. As shown in Fig. 1, subjects willing to consider enrollment are consented prior to invasive evaluation. Subjects undergo V/Q scan, right-heart catheterization, and pulmonary angiography for definitive diagnosis of CTEPH by the standard practice based on ESC guideline recommendation [3]. The identified CTEPH patients are provisionally enrolled in this study. An independent experienced PEA surgeon determines if subjects are eligible for PEA. If the subjects are deemed technically operable, they are excluded from this study. All patients who meet the inclusion criteria but don’t meet the exclusion criteria are randomly divided into two groups with 2:1 rate via a randomization application and are observed for 12 months. One group is treated with riociguat only, namely the riociguat group (R group); the other group is given additional BPA therapy on the basis of 3 months riociguat treatment, which is riociguat + BPA group (R+B group). Riociguat tablets are administered orally to all randomized patients at starting dose of 1.0 mg TID and are increased by 0.5 mg increments in 2-week intervals to 1.5, 2.0, and 2.5 mg TID (maximum total daily dose: 7.5 mg) if systolic blood pressure (SBP) is ≥ 95 mmHg and there are no signs or symptoms of hypotension. If higher doses are not tolerated, patients are maintained on lower doses (minimum allowed dose: 0.5 mg TID). After the end of the 8-week titration phase, riociguat is continued at the optimal individual dose for 4 weeks. In the R+B group, patients receive 4 times BPA in 2–3-week intervals in the following 3 months according to the morphology of the pulmonary lesion evaluated by preoperative right-heart catheterization and pulmonary angiography. In general, 3 vessels are performed each time. However, at least among the collaborative institutions included in this study. PEA-inoperable patients are very rarely considered unsuitable for BPA, because the institutes are professional BPA centers in China. Then all participants are followed up to 12 months. And the safety follow-up is up to 30 days later the study completion.

**Fig. 1 Fig1:**
[figure not shown]
Flow diagram of study recruitment and randomization. After obtaining consent and diagnosis of chronic thromboembolic pulmonary hypertension is confirmed, subjects will be randomized into either the B+R or R group, to receive treatment for 12 months. Patients in the B+R group receive 4 times BPA 3 months later initial riociguat in 3 months. Observations will be recorded at the time of screening/baseline and at 3, 6, and 12 months after the initiation of treatment. BPA, balloon pulmonary angioplasty; CTEPH, chronic thromboembolic pulmonary hypertension

Observations are made at the time of screening or baseline and 3, 6, and 12 months after initial treatment. All BPA procedures are performed by two specific surgeons who are blinded to the trial, and echocardiography, 6MWD, and cardiopulmonary exercise testing are performed by specific experienced physicians who are blinded to the trial.

Data processing of patients who withdraw from the study or terminate the study uses the last measured value (LOCF) before withdrawal for statistical analysis. Table 1 shows the schedule of assessments performed at each visit for each treatment group, including mandatory and optional assessments.

**Table 1 Tab1:** Schedule of visits and observation items for enrolled subjects

Observation items	Visit 1 Screening/baseline	Visit 2 3 months ± 7 days	Visit 3 6 months ± 7 days	Visit 4 12 months ± 7 days
Informed consent	X			
Inclusion/exclusion	X			
Demographics	X	X	X	X
Medical history	X	X	X	X
vital signs	X	X	X	X
Laboratory tests	X	X	X	X
Blood gas test	X	X	X	X
electrocardiogram	X	X	X	X
6MWD	X	X	X	X
WHO-FC	X	X	X	X
Pulmonary function	X			X
Echocardiography	X		X	X
RHC	X			X
CPET	X		X	X
CMR	X		X	X
QOL (SF-36)	X	X	X	X
Concomitant medication	X	X	X	X
Medication adherence		X	X	X
Adverse events	X	X	X	X

*6MWD* 6-min walk distance, *WHO-FC* World Health Organization functional class, *RHC* right-heart catheterization, *CPET* cardiopulmonary exercise testing, *CMR* cardiac magnetic resonance, *QOL* quality of life

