### Outcome measure

The primary endpoint is the change in pulmonary vascular resistance between baseline and 12 months. Secondary endpoints include several clinical and quality-of-life parameters (as detailed in Table 2).

**Table 2 Tab2:** Secondary endpoints, exploratory endpoint and safety evaluation that will be measured and/or compared at baseline and at 12 months after initiation of treatment

Secondary endpoints	
Change in hemodynamic variables	mean pulmonary arterial pressure, cardiac output, etc.
Change in 6-min walk distance	
Change in WHO functional class	
Change in plasma NT-proBNP level	
Change in echocardiography	tricuspid annulus systolic displacement (TAPSE), right atrium area, right ventricle size, eccentricity index, pericardial effusion
Change in Borg dyspnea index	
Change in quality-of-life parameters (SF 36)	

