**Safety evaluation**	
Frequency of adverse events	hemoptysis/pulmonary hemorrhage (vascular perforation, vascular dissection, vascular rupture, etc), pneumothorax, hypotension, pulmonary congestion/ pulmonary edema, late-onset lung disturbance, heart failure, pneumonia, headache, dizziness, peripheral edema, nausea/vomiting, retching, diarrhea, nasopharyngitis, upper respiratory inflammation, respiratory distress, coughing and fainting
Clinical worsening during the observation period and time to clinical worsening	All-cause mortality, heart/lung transplant, hospitalization due to clinical worsening, new initiation of pulmonary hypertension target medications, worsening of 30% or greater from baseline in the 6MWD and persistent worsening in the WHO FC from baseline due to the worsening of a primary disease.
Laboratory tests	hemoglobin, alanine aminotransferase, creatinine, aspartate aminotransferase

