### Data collection and management

The investigators who enter information into the case report form (CRF) are responsible for ensuring the accuracy and completeness of information. The investigators must save the CRF and all the original data. According to CRF data, a database is established through Epidata software. Data collection and management are carried out by physicians who are blinded to this trial to avoid bias. Linkable anonymization by central registration number is used to identify the subjects and only the subject number is recorded in the case report form. Moreover, when a patient’s name appears in any other document (such as a pathology report), the name must be hidden before providing a copy of the document. The investigators are responsible for the appropriate storage of the correspondence table prepared by them to identify the subjects. This correspondence table must be retained for 5 years after completion of this study. Appropriate measures, such as encoding or deletion, are taken to ensure that the subjects cannot be identified in any display or public disclosure of information related to this study, in accordance with applicable laws and regulations. If data are transmitted over an unsecured electronic network, the data must be encoded at the source. Representatives of the clinical research office, ethics committee/institutional review committee, and relevant supervision and management departments have the right to inspect medical records to verify the collected data. During the inspection process, the above-mentioned personnel strictly follow the local data protection laws to keep the subjects’ personal information confidential.

If the results of the study are published publicly, the information confirming the identity of the subject remains confidential.

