### Strengths and limitations of this study

This is a randomized controlled trial comparing the efficacy and safety of BPA combined with riociguat and riociguat alone in patients with inoperable chronic thromboembolic pulmonary hypertension. This study evaluates the efficacy and safety of BPA combined with riociguat over a relatively long period (12 months). This is the first study to compare the efficacy and safety between BPA combined with riociguat and riociguat alone.

The main limitation of this study is the open-label trial design. Because there is no distinct criterion for BPA in each lesion, operators are aware of the mean pulmonary vascular resistance (the primary endpoint in this study), and they might be incentivized to continue BPA. Thus, the bias for the BPA operators cannot be completely avoided. However, since this study compares medical and surgical treatment, it is difficult to use a placebo or mask patients and/or physicians. Other limitations of this study include single-center design and a relatively small number of subjects are recruited.

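### Blinded grading of WHO functional class is not secured, although it is a judgement-based secondary endpoint and a clinical-worsening component in an open-label trial

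*Protocol article*

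**What the plan says.** All references are to the protocol article.

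- **Blinded assessments** (Methods and analysis, Design): "echocardiography, 6MWD, and cardiopulmonary exercise testing are performed by specific experienced physicians who are blinded to the trial". WHO-FC is not mentioned.
- **Role as endpoint** (Outcome measure, Table 2): "Change in WHO functional class" is a secondary endpoint. The secondary hypothesis is that the combination "significantly improves activity tolerance including 6-min walk distance, WHO functional class, SF-36 compared with riociguat alone".
- **Role in clinical worsening** (Table 2, safety evaluation): one listed component is "persistent worsening in the WHO FC from baseline due to the worsening of a primary disease".
- **Masking of the trial** (Strengths and limitations of this study): "The main limitation of this study is the open-label trial design".
- **Data handling** (Data collection and management): "Data collection and management are carried out by physicians who are blinded to this trial to avoid bias". The same section also says: "The investigators who enter information into the case report form (CRF) are responsible for ensuring the accuracy and completeness of information".

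**The concern.** WHO-FC is a clinical grade built on reported symptoms, so a grader who knows the treatment arm can be influenced by it. The worsening component adds a second judgement, because the deterioration must be attributed to the underlying disease. The Design section names blinded assessors for a walk test and two instrument-based tests, but names none for this more subjective outcome.

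If the grader knows who had BPA, improvement could be over-recorded in the combination arm and worsening under-recorded. That would bias one part of a secondary hypothesis and one component of the worsening composite. An analysis plan cannot repair it later, because the bias enters when the grade is given at the visit.

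**Working it through.** **1. Is blinded grading of WHO-FC stated anywhere?**

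| Place in the article | Who is blinded, or who acts | Does it cover WHO-FC grading? |
|---|---|---|
| Design | Physicians doing echocardiography, 6MWD and CPET | No, WHO-FC is not named |
| Data collection and management | Physicians collecting and managing data, in general terms | Not assigned; the section concerns the CRF, the database and anonymisation |
| Data collection and management | Investigators enter the CRF | No grader is named |
| Statistical analysis | The analyst | No, this concerns analysis only |

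No section names the person who grades WHO-FC.

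**2. Is a blinded physician already present when WHO-FC is graded?** Table 1 schedules both WHO-FC and 6MWD at baseline, 3, 6 and 12 months. The overlap with the 6MWD is complete. Echocardiography and CPET are scheduled at baseline, 6 and 12 months only, so they would not cover month 3.

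**3. The plan's own figure.** The arm sizes used below are the 54 and 27 in the Sample size section, and they reproduce. With a difference of 4.5 − 2.8 = 1.7 WU, SD 2, 2:1 allocation, two-sided 0.05 and 90% power, a t-test needs 46 + 23 = 69 patients (power 0.907). Allowing for 15% dropout, 69 / 0.85 = 81.2, in line with the stated 81. The present point does not depend on this calculation.

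**4. Illustration of size.** The article gives neither a WHO-FC improvement rate nor an observer shift, so both are assumed. Let p be the probability of improving by at least one class in both arms (no true difference), and s the grader shift in favour of the combination arm. The chance of a significant result for that arm is

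P = Σx Σy Bin(x; 54, p + s) · Bin(y; 27, p), summed over tables with two-sided Fisher p < 0.05 and x/54 > y/27.

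| Assumed shift s (points) | p = 0.35 | p = 0.40 |
|---|---|---|
| 0 | 1.7% | 1.6% |
| 5 | 4.4% | 4.3% |
| 10 | 9.9% | 9.9% |
| 15 | 19.5% | 19.6% |
| 20 | 33.6% | 33.8% |

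With 15% fewer patients (54 × 0.85 ≈ 46 and 27 × 0.85 ≈ 23), shifts of 10, 15 and 20 points give about 11%, 19-20% and 30-32%. The article does not fix a test for change in WHO-FC, so Fisher's test is also an assumption.

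**The case against.** The strongest objection is the general sentence on blinded data collection. Read broadly, it could include WHO-FC, and a journal article may leave the choice of grader to the full protocol. Part of this stands. A reader might infer that WHO-FC is graded by unblinded investigators, and the document does not support that, because no grader is named. But the general sentence does not settle the matter the other way. It sits among data-handling provisions and beside CRF entry by investigators. If it already meant that every outcome is graded blind, the specific list in the Design section would not be needed. Since the article chose to state which assessments are blinded, the omission is worth resolving.

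A second objection is that masking is not feasible. The limitations section calls it difficult to mask patients or physicians, but that remark concerns the treatments compared. The Design section shows that outcome assessors can be masked.

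Third, patients know whether they had BPA and report their own symptoms. This stands. Blinding the grader removes only the grader's share of the bias, and the illustration attributes the whole shift to the grader. The same limit applies to the 6MWD, which the plan nevertheless blinds.

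A reader might also extend the point to the Borg index and the SF-36. The article does not support that. The Borg index has no row of its own in Table 1, and if it is recorded with the 6MWD or CPET, those tests are already done by blinded physicians. The SF-36 is reported by the patient, so a blinded grader would not change it.

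**Conclusion.** The point holds as a gap in assurance: the article does not secure blinded grading for a judgement-based outcome with roles in a secondary endpoint, a secondary hypothesis and the worsening composite. It does not show that grading is unblinded or that bias has occurred.

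The reach is limited. The primary endpoint, change in pulmonary vascular resistance measured at right-heart catheterisation, is unaffected. WHO-FC is one of six listed worsening components, and the 6MWD component already rests on a blinded test. No size was worked out for the composite.

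The percentages above show only how sensitive a comparison of this size is to grader shift. They rest on assumed improvement rates, assumed shifts and an assumed test, and should not be quoted as estimates for this trial. The change is worth making because it removes an avoidable source of bias with staff already in place.

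**What to change.** 1. In the Design section, add WHO-FC to the blinded assessments. It should be graded at visits 1 to 4 by the blinded physician who already performs the 6MWD, without access to BPA records.
2. For the clinical-worsening composite, have an existing blinded physician decide whether the WHO-FC component is met, including its attribution to the underlying disease.
3. Align Data collection and management with this: say which outcomes the blinded physicians record and what the investigators enter in the CRF.

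The cost is a wording change and a few minutes per visit. No additional visits, staff or patients are needed. Because a patient may reveal the arm and symptoms remain self-reported, the report should describe the blinding of WHO-FC as partial.
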